### Randomization, blinding and concealment

We will utilize randomization to assign participants to the three groups. A RA, independent from the recruitment and intervention process, will open sequentially-numbered, opaque sealed envelopes, each containing a card indicating the allocated group. The random numbers used for group assignment will be generated in advance by another RA using a personal computer, ensuring allocation concealment. Modifying allocated interventions will not be allowed. However, the participants’ participation will be totally voluntary. They can withdraw at any time without penalty. Also, the participants can withdraw if they report any adverse event, e.g., psychological discomfort. Because smoking cessation is not part of routine care, and most instruments use self-report, blinding is not possible.

### Contamination

Because subject recruitment will be conducted in various smoking hotspots at different times, participants will be unlikely to know each other to exchange information. The possibility of contamination is low.

### Data collection

Participants will be recruited from smoking hotspots in Mong Kok. Smoking hotspots are places where many smokers congregate [31]. Mong Kok is one of the most popular places among Hong Kong youth, including young smokers [35]. The RA will approach smokers who smoke in selected smoking hotspots to deliver leaflets containing information of the study. If smokers are willing to participate, the RA will check their eligibility. Eligible smokers will be invited to join. For smokers who are ineligible or refuse participation, the RA will remind them of the health effects of smoking and drinking and refer them to the government’s quit line. The timeline of this study was presented in S2 File.

Data will be collected at baseline, 1 week, 1 month, 3 months, and 6 months, which are data collection timepoints that are commonly used in smoking cessation trials [4,19,20,31]. All participants will complete a structured questionnaire at each timepoints via telephone. Self-reported quitters at 6 months will be invited for biochemical validation.

Participants in the II arm with high (80%–100%) and low (0%–20%) adherence will be purposively selected for one-to-one, 20–30 minutes, semi-structured interviews to further assess the feasibility of II. All interviews will be conducted by the RA in a meeting room of a local university following a semi-structured interview guide and will be audio recorded. Sample size will be determined by data saturation. Based on previous smoking cessation studies [4,16], we expect data saturation to occur after interviewing 30 participants: 15 from the high adherence group and 15 from the low adherence group. As one outcome of this study is to test the feasibility of the II, no incentive will be provided to the participants.

The audit will be conducted by one auditor who was blinded to experimental or control sites. She will regularly audit the overall quality and completeness of the data, examine source documents, interview investigators and coordinators, and confirm that the clinical center has complied with the requirements of the protocol.

### Data analysis

The first objective, examining the feasibility of the II will primarily be determined by quantitative data. Qualitative data will be used to further explain the intervention feasibility. Quantitative data will be analyzed using SPSS. Descriptive statistics, i.e. frequency and percentage will be used to report the feasibility measures, including screening rate, eligibility rate, consent rate, randomization rate, attendance rate, adherence to the intervention, retention rate, completion rate, missing data and adverse events. Qualitative data will be analyzed by the traditional text analysis method using content analysis. We will use double data entry and manual checking of frequencies during data cleaning to ensure the data quality. The semi-structured interviews will be immediately transcribed and returned to informants to check for accuracy. Two team members will read the transcripts to obtain a general sense of the interviews and separately identify important statements, which will be merged into themes and subthemes. Discrepancies during analyses will be resolved in research meetings. Findings will be returned to informants for comment. Qualitative results will be reported according to Consolidated Criteria for Reporting Qualitative Research. A coding frame with quotations will be used to present results.

For the second objective, calculating the effect size of II, we will use quantitative data collected by the structured questionnaire. The three arms will be compared using analysis of variance for continuous variables and chi-square test for categorical variables. When there are violations of the normality/Gaussian assumptions in the data, alternative methods including non-parametric tests such as Kruskal-Wallis test, transformation of data and robust methods will be considered to assess the three arms, instead of ANOVA. Furthermore intention-to-treat will be applied. Participants lost to follow-up will be regarded as smokers who have the same cigarette consumption at baseline. Effect sizes of II for self-reported and biochemically validated quit rates at 6 months will be determined using the generalized estimating equation (GEE) model after controlling for baseline characteristics, relative to ST and control groups. The GEE model will be built (based on the goodness of fit) after checking for multicollinearity among the identified variables. We will apply the principle of intention to treat. Missing data will be handled by multiple imputations. The data monitoring committee (DMC) will not be set up for this study, as this trial does not involve significant safety concerns [36]. No interim analyses for efficacy will be performed during the study.

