Standard treatment based on the ‘5A’ and ‘5R’ models proposed by the World Health Organization is recommended as a common smoking cessation intervention [15–20]. This was chosen as a comparator because we wanted to determine whether II is more effective than the current smoking cessation practice. Additionally, usual care, i.e., leaflet related to smoking cessation and alcohol drinking, was also chosen as another comparator because it only has minimal effect on smoking cessation outcomes [21]. This could maximize the comparison to show the intervention effect of II. We hypothesize that an integrated smoking cessation and alcohol intervention that aims to cease both behaviors will be more effective in helping young smokers to achieve self-reported and biochemically validated abstinence at 6 months compared with the standard treatment based on the ‘5A’ and ‘5R’ models and the control that is receiving leaflets related to smoking cessation and alcohol drinking. This hypnosis is based on our reasoning that the II will remove smokers from drinking environments that support smoking and eliminate smoking cues. As such, we will conduct a 3-arm (1:1:1), superior, parallel, non-blind, randomized controlled trial to test the feasibility and preliminary effectiveness of integrated smoking cessation and alcohol interventions in young Hong Kong Chinese smokers.

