### Outcome

The primary outcomes are feasibility measures: screening rate, eligibility rate, consent rate, randomization rate, attendance rate of intervention, adherence to intervention protocol, retention rate, completion rate, missing data, and adverse events. The secondary outcomes are effect size of II on self-reported and biochemically validated quit rates at 6 months relative to control and ST. These quit rates are the most useful outcomes to show the effectiveness of smoking cessation interventions [21]. Six months was chosen because it is the gold standard follow-up duration for evaluation in smoking cessation trials [4,15–20,31].

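### Blinding is called impossible for reasons that do not reach the analyst, while the GEE for the quit-rate effects is built on fit: coded arms until model lock would be a cheap improvement (minor)

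*Protocol article*

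**What the plan says.** Three parts of the protocol article bear on this point.

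- **Blinding.** Under Randomization, blinding and concealment: "Because smoking cessation is not part of routine care, and most instruments use self-report, blinding is not possible". The Theoretical framework section labels the design in the same way: "we will conduct a 3-arm (1:1:1), superior, parallel, non-blind, randomized controlled trial". The Data collection section nevertheless describes one masked role: "The audit will be conducted by one auditor who was blinded to experimental or control sites". No section mentions the analyst.
- **Analysis.** The Data analysis section sets defaults: "The three arms will be compared using analysis of variance for continuous variables and chi-square test for categorical variables". If normality fails, "alternative methods including non-parametric tests such as Kruskal-Wallis test, transformation of data and robust methods will be considered" instead of ANOVA. The effect of the integrated intervention (II) on quit rates is to be "determined using the generalized estimating equation (GEE) model after controlling for baseline characteristics, relative to ST and control groups", and "The GEE model will be built (based on the goodness of fit) after checking for multicollinearity among the identified variables". The Sample section commits two covariates to that model, nicotine dependence and heavy drinking. The remaining covariates are not listed.
- **Outcomes.** Under Outcome: "The primary outcomes are feasibility measures". The II effect sizes on 6-month quit rates are secondary.

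**The concern.** The blinding sentence has no qualifier, yet its two reasons apply only to people who receive or deliver the intervention or report outcomes. Nothing in them prevents an analyst from receiving a file with the arms coded.

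This matters because the GEE that yields the II effect is not fixed. It is built on fit after a collinearity check, from a covariate set that is only partly named. If whoever builds it can see which arm is II, knowledge of the arms can enter the choice of model. The protocol expects II to do better, and the Discussion says a full-scale trial will follow from these results, so an effect size tilted towards II would carry forward. The ANOVA replacements leave a similar freedom, but only for continuous variables.

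**Working it through.** **1. Whom the stated reasons reach**

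| Role | Do the stated reasons apply? | What the protocol says |
|---|---|---|
| Participants | Yes: they know what they receive and they self-report | Not blinded |
| RA delivering the intervention | Yes | Not blinded |
| Auditor | No | Blinded |
| Analyst | No | Not mentioned |

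**2. Which choices are left to the data**

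| Outcome | Fixed | Left open |
|---|---|---|
| Quit rates (binary) | Chi-square; GEE; two covariates | GEE form and other covariates, chosen on fit |
| Continuous variables | ANOVA | Its replacement if normality fails; no diagnostic or order given |

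Only the first row concerns the II effect on quitting.

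**3. How far could visible arms move the result?** The plan gives no figure on this, so there is none to reproduce. From the plan: 50 per arm and 5% alpha. Everything else below is an assumption.

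- *Model.* Two arms and no treatment effect. logit P(quit) = logit(p0) - 0.5·C1 + 0.3·C2 - 0.4·C4, with C3 having no effect. C1 to C3 are standard normal and C4 is binary. p0 is 10% or 20%. There are 1,500 null trials for each p0.
- *Analysis.* Logistic regression with robust standard errors stands in for the longitudinal GEE. The fixed analysis uses all four covariates. The steered analysis takes the smallest treatment p-value over all 2^4 = 16 covariate sets.
- *Result.* p0 = 10%: 4.5% fixed, 7.0% steered. p0 = 20%: 4.9% fixed, 6.9% steered.

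**4. Respecting the two committed covariates.** With two of the four covariates always in the model, 2^2 = 4 sets remain. Dropouts are counted as smokers, with 15% assumed missing (the plan assumes 10% attrition) and a quit rate of about 20-22%. Over 2,000 null trials per scenario, one fixed model rejected in 5.1-5.4% and the smallest p-value in 6.5-7.7%. A separate run under the same restriction gave about 6% for the smallest p-value.

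**5. Continuous outcomes.** For a skewed outcome in three arms of 50 (4,000 null trials), ANOVA, Kruskal-Wallis and ANOVA on logs each rejected in 3.9-4.3%. The best of the three rejected in 6.7%.

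**6. Precision.** With 1,500 trials the simulation standard error is √(0.05 × 0.95 / 1500) = 0.0056 near 5% and √(0.07 × 0.93 / 1500) = 0.0066 near 7%. The figures should be read to about one percentage point.

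**7. Sample size.** The remedy leaves it unchanged: 45 / (1 - 0.10) = 50 per arm, and 3 × 50 = 150.

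**The case against.** The strongest reply is that the blinding sentence, read in its paragraph on allocation and withdrawal, is naturally about participants and the RA. Analyst masking is commonly left to an analysis plan, and this is a condensed article. That has force: silence about the analyst alone would be no finding. What remains is an unqualified statement that a masked analyst would contradict, together with a written rule that the model for the II effect is built on the data.

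Other parts of the reply stand. Goodness of fit is not the same as picking the smallest treatment p-value, so the simulated figures are an upper limit within their setting. The normality trigger can be checked without arm labels. Fixing the GEE form in advance would remove the freedom even without masking. The primary outcomes are descriptive and untouched.

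Three stronger readings are tempting, and the documents do not support them:

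- *That the protocol rules out all blinding.* The blinded auditor shows otherwise. Nor does the text say that the analyst will see the arms; it only fails to prevent it.
- *That the ANOVA fallback list can steer the quit-rate effect.* Quit rates are binary and go to chi-square and GEE.
- *That steering doubles the false-positive rate.* Rates of about 10-12% do arise over 32 versions (16 covariate sets × 2 missing-data treatments). But that count includes complete-case analysis, which the protocol does not name, and models that omit the two committed covariates. The protocol itself names two treatments, counting dropouts as smokers and multiple imputation. Any tension between them is a separate matter that masking would not resolve.

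**Conclusion.** The point holds as a minor one. The stated reasons for not blinding do not extend to the analyst, and the GEE for the quit-rate effects is chosen on the data with nothing to keep the arms hidden. The illustrative upper limit of steering is a type I error of about 6-8% against about 5% for one fixed model.

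This rests on four candidate covariates of assumed strength, quit rates of about 10-22%, and a single-time logistic model in place of the GEE. A larger covariate pool or a free choice of working correlation could raise the figure, and keeping to the fit criterion would lower it; neither was simulated. The exposure is confined to the secondary effect sizes. Masking the analyst would not cure bias from unblinded self-report.

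**What to change.** **Randomization, blinding and concealment.** Limit the statement to participants and the RA, and add that the analyst works with coded arms until the analysis is locked.

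**Data analysis.** Give the analyst a file with arms labelled A/B/C and the II-only fields (AUDIT results, alcohol booster records) removed. On that file, settle and date the GEE form, the covariates (keeping nicotine dependence and heavy drinking, as the Sample section commits) and any replacement for ANOVA. Then release the codes, held until then by the RA who generated the random numbers. Tabulate attendance and adherence separately, since both are defined only for the two treatment arms and would reveal the control arm.

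**Cost.** One coded file and one dated note, with no added staff or participants. Masking may be imperfect if one arm stands out in the data.

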### Sample

Individuals are eligible for the study if they are (1) aged 18 to 25 years, (2) smoked at least one cigarette in the past 30 days, (3) consumed at least one cup of alcohol (10 ounces of beer, 4 ounces of wine, or 1 ounce of liquor) [4] in the past 30 days, and (4) speak Cantonese. Exclusion criteria include: (1) have cognition and/or communication problems, (2) have clinically reported mental disorders (anxiety, depression, etc.), (3) current use of nicotine containing medication, (4) participating in other smoking cessation interventions including pharmacological interventions. We will target participants aged 18–25 years because this age range is considered young adulthood [22]. Smokers aged <18 may also have alcohol drinking; however, their psychosocial development differs from those who reach the age of majority [23]. Therefore, we only targeted those aged 18–25 years to ensure the homogeneity. As this study aims to explore the feasibility and preliminary effect of II on smoking cessation among young smokers, we do not set any restriction on nicotine dependency. Hence, light and heavy smokers will be included. This variable will also be controlled in our GEE model. However, non-smokers will not be included. Similarly, we will not set any restriction on the participants’ alcohol dependency. However, participants will be categorized as heavy drinkers when exceeding the following threshold: drinking on a maximum of 5 days per week, maximum 3 glasses per day and 14 per week for women, and maximum five glasses per day and 21 per week for men [24]. This variable will also be controlled in the GEE model. According to Department of Health, Hong Kong [25], regular drinkers are defined as those who drink at least once in 7 days, whereas occasional drinkers are those who drink once in 30 days. We will include occasional drinkers because occasional drinking can also lead to smoking lapses and relapses [4].

There is no fixed rule for calculating sample size for a pilot study [26]. Based on the sample size estimation guide for pilot studies outlined by Birkett and Day [27]. 50 participants per arm will provide 80% power to detect differences between the groups, assuming a 5% alpha error and a 10% attrition rate. Hence, a total of 150 participants will be recruited for this study.

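### Two missing-data rules without stated scope both cover a missing 6-month quit status, and quitters who skip validation fall only under imputation

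*Protocol article*

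**What the plan says.** All the analysis rules stand in one paragraph of the protocol article, in the Data analysis section under the second objective. In order:

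- Intention to treat is invoked, followed by the rule for losses: "Participants lost to follow-up will be regarded as smokers who have the same cigarette consumption at baseline".
- The estimator for the secondary outcomes is named: "Effect sizes of II for self-reported and biochemically validated quit rates at 6 months will be determined using the generalized estimating equation (GEE) model", adjusted for baseline characteristics.
- Intention to treat is invoked again ("We will apply the principle of intention to treat"), followed by a second rule: "Missing data will be handled by multiple imputations".

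The Sample section gives the only loss figure, "assuming a 5% alpha error and a 10% attrition rate", with 50 participants per arm. The Data collection section says "Self-reported quitters at 6 months will be invited for biochemical validation". It gives no expected attendance, and the article does not say how a self-reported quitter who does not attend is classified.

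**The concern.** Within one analysis, a lost participant's 6-month status can be fixed as smoker or drawn from an imputation model, but not both. The two sentences serve the same objective, each follows a statement of intention to treat, and nothing says which variables, which kind of non-response or which analysis each one governs. The point estimate and its standard error depend on the choice: fixing the value treats it as known, while multiple imputation adds uncertainty for it.

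The validated outcome has a second source of missing data. Someone who answers the 6-month call, reports having quit and then does not come for the carbon monoxide and cotinine tests has not been lost to follow-up. The smoker rule does not reach that person; the imputation sentence does. The imputation would learn from those who chose to be tested. If people who expect to fail stay away, unverified quitters would be counted as validated.

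The quit rates are secondary, but they are the trial's efficacy outputs, and the Discussion says that a full-scale trial will follow on the basis of the results.

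**Working it through.** **Inputs.** From the Sample section: 50 per arm and 10% attrition (m = 0.10). The article gives no quit rates, loss by arm or validation attendance, so these are assumed below and labelled as such.

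**The plan's own figures.** 45 / 0.9 = 50 per arm and 3 × 50 = 150, so the attrition allowance is consistent. The 80% power cannot be reproduced, because no effect size or quit rates are given. This point does not rest on it.

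**1. Quit rate in one arm.** Let q be the quit rate among those observed and m the share lost.

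- Lost = smoker: q(1 − m).
- Multiple imputation with data missing at random: about q.
- Ratio: 1/(1 − m).

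At m = 0.10 the ratio is 1/0.9 = 1.11. With an assumed 9 quitters among 45 respondents, the rates are 9/50 = 18% and about 9/45 = 20%. At other assumed losses the ratio is 1.05 (5%), 1.25 (20%), 1.43 (30%) and 2.00 (50%).

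**2. Effect between arms.** Assumed observed rates are 20% (integrated intervention) and 10% (control). Imputation gives RR = 2.0 and OR = (0.20/0.80)/(0.10/0.90) = 2.25 throughout.

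| Assumed loss, intervention v control | Rates with lost = smoker | RR | OR |
|---|---|---|---|
| 10% v 10% | 18.0% v 9.0% | 2.00 | 2.22 |
| 15% v 5% | 17.0% v 9.5% | 1.79 | 1.95 |
| 5% v 15% | 19.0% v 8.5% | 2.24 | 2.53 |

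For the second row, OR = (0.17/0.83)/(0.095/0.905) = 1.95. For the third, OR = (0.19/0.81)/(0.085/0.915) = 2.53. With equal 10% loss the risk difference moves from 10.0 to 9.0 points and the ratio measures hardly at all. Unequal loss moves the odds ratio in either direction, so the smoker rule lowers each arm's rate without necessarily being conservative for the comparison.

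**3. Validation non-attenders.** Here the lost are set to smoker in both calculations. Let S be the self-reported quitters, a the share who attend, p the pass rate among attenders and N the number randomised.

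- Non-attenders imputed at the attenders' pass rate: S·p/N.
- Non-attenders counted as not validated: S·a·p/N.
- Ratio: 1/a.

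For assumed attendance of 100%, 80%, 60% and 40% the ratio is 1.0, 1.25, 1.67 and 2.5. In counts, with S = 9, five attending and all five passing, the rates are 9/50 = 18% and 5/50 = 10%, a ratio of 9/5 = 1.8.

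**The case against.** The strongest reply is that the sentences can coexist. One is specific to people lost to follow-up. The other is general, comes after a covariate-adjusted model, and may be meant for skipped items and covariates. A condensed article may also leave the split between main and sensitivity analysis to an analysis plan that is not shown. It stands that the rules are not contradictory in principle; a scope statement would reconcile them. It does not stand that the matter is only deferred, because the article states both rules for the same outcomes and gives no such scope. Nor can it be said that the choice will be made after seeing the data, since a fuller plan may settle it.

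A reader might infer that the two rules give quit rates differing twofold. The documents do not support that. At 10% attrition the gap is 1.11-fold, and twofold for the self-reported rate needs 50% loss. For the validated rate at 10% attrition it needs attendance of about 56% (1/(0.9 × 0.556) = 2.0) and also a rule counting non-attenders as not quit, which the plan does not state. Under the rules as written, with the lost set to smoker and non-attenders imputed, the example gives 9/50 = 18%, against 9/45 = 20% for full imputation: again 1.11.

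A reader might also take "no incentive will be provided to the participants" as showing that validation attendance will be poor. That sentence closes the paragraph on the qualitative interviews and does not mention validation.

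Finally, the primary outcomes are feasibility measures reported descriptively, and this point does not affect how they are analysed.

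**Conclusion.** The point holds as a gap in scope. The main analysis of both secondary quit-rate outcomes is not determined, because two unrestricted rules cover a missing 6-month status.

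The consequence is modest at the plan's own attrition: about 1.11-fold in each arm's rate, and almost nothing on the ratio scale if loss is equal. It becomes material with unequal loss, where the odds ratio is 1.95 or 2.53 against 2.25. Those values rest on assumed observed rates of 20% v 10%, assumed loss of 15% v 5%, and imputation that reproduces the observed rate within each arm.

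The handling of validation non-attenders is a separate weakness and may be the larger one: 1.0 to 2.5 times over assumed attendance of 100% to 40%, if they are imputed at the attenders' pass rate. That range compares the plan as written with a stricter rule it does not contain; it is not a gap between its two stated rules. The trial can go ahead without this change, but the change should be made before the quit rates are analysed.

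**What to change.** State one hierarchy in the Data analysis section:

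- **Main analysis:** keep all randomised participants in the denominator and count a missing 6-month status as not quit. For the validated outcome, count a self-reported quitter without completed carbon monoxide and cotinine tests as not validated.
- **Multiple imputation:** in the main analysis, limit it to missing baseline covariates and questionnaire items. Use it for quit status only in a sensitivity analysis.
- **Reporting:** give validation attendance by arm, so that readers can judge how far the validated rate depends on it.

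This keeps the plan's own smoker rule. The baseline-consumption part of that rule need not change, since consumption is not one of the named outcomes. The cost is a few sentences, one extra sensitivity analysis and lower, more conservative quit rates. Recruitment, visits and interventions are unaffected.
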